**Table 2 T2:**
[figure not shown]
Dose parameters used in the protocol of the application of analgesia with light-emitting diode therapy.

### Control group: bath therapy

2.6

The method of analgesia with the bath therapy will be performed using a hot shower at 37°C for 10 minutes. After showering the entire body or the back for 5 minutes, the participants will be allowed to direct the water flow to any area of the body that feels the most comfortable and to adjust the temperature themselves for improved comfort. Bath therapy will be performed at 3 time points during labor: at cervical dilatation of 4–5 cm, 6–7 cm, and 8–9 cm. Data on the level of pain, membrane characteristics (intact or damaged), heart rate, cardiotocography, and uterine dynamics will be collected after the bath therapy by performing the same measurements used in the intervention group.

### Data analysis

2.7

The distribution of the VAS scores will be analyzed, and the continuous variables with normal data distribution will be compared using the *t* test and expressed as mean ± standard deviation. The categorical variables will be analyzed using the *χ*^2^ test or Fisher exact test. Non-normal data will be analyzed using the Mann–Whitney *U* test. All analyses will be performed using the statistical software SPSS version 20.0 for Windows (IBM Corporation, USA) at a level of significance of 5%.

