**Table 1 T1:**
[figure not shown]
Schedule of enrolment, interventions, and assessments of treatments.

The participants will be randomized into 2 groups: intervention group [analgesia with LED therapy (n = 30)] and control group [analgesia with bath therapy (n = 30)]. The perception of pain will be evaluated using the visual analogue scale (VAS) with a score from 0 to 10 at baseline, that is, before the intervention. In both the groups, the procedure will last 10 minutes at each of 3 time points during labor: cervical dilation of 4 to 5 cm, 6 to 7 cm, and 8 to 9 cm.^[33]^ At the 3 time points, the level of pain will be assessed using VAS shortly after the intervention. Pharmacological analgesia will be promptly performed whenever necessary; in these cases, the participant will be excluded from the study and replaced with another consecutive participant.

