### Objectives of the study

2.2

Primary objective: To evaluate the effect of LED photobiomodulation on analgesia during labor as an alternative nonpharmacological intervention.

Research hypotheses:

Hypothesis 0 (null): the use of LED photobiomodulation exerts an analgesic effect similar to that of the bath therapy.

Hypothesis 1: the use of LED photobiomodulation exerts an analgesic effect superior to that of the bath therapy.

Hypothesis 2: the use of LED photobiomodulation exerts an analgesic effect inferior to that of the bath therapy.

Secondary objective: To evaluate fetal conditions using cardiotocography and the Apgar score in the first and fifth minutes after birth, and the level of satisfaction with the experience of childbirth using a questionnaire.

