### Participants

2.3

The study participants will be women aged >18 years, who are expected go into natural labor in the Maternity Hospital of Mandaqui. The inclusion criteria for the study will be as follows: women who request analgesia during labor; nulliparous and multiparous women; women with term gestation; women without previous diseases, including diabetes, neurological diseases, and metabolic diseases; and women in whom it is possible to evaluate fetal vitality during analgesia.

The exclusion criteria will be as follows: women whose labor is induced with medications; women who request drug analgesia during labor; and women who undergo cesarean delivery.

The participants will be recruited on admission at the maternity hospital and will be randomized in the 2 study groups after clarifying regarding the study objectives and obtaining their informed consent.

The sample size has been estimated using the difference in means in the score of the VAS from a study that evaluated analgesia during labor.^[34]^ The difference in the mean VAS score between the groups was set as 2 (standard deviation: 1.6). The minimum number of participants considering a power of 80% and level of significance of 5% was 28, and the minimum number of participants per group considering possible exclusions was 30.

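### Three post-treatment pain scores, no single deciding comparison and no use of baseline VAS: section 2.7 should name one primary comparison, because the 5% level is not held if any one stage could decide

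*Protocol article*

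**What the plan says.** - **Measurements.** Section 2.1 (and the Abstract) has VAS 0-10 scored at baseline, then after treatment at 4-5, 6-7 and 8-9 cm: "At the 3 time points, the level of pain will be assessed using VAS shortly after the intervention".
- **Objective.** Section 2.2 is general: "To evaluate the effect of LED photobiomodulation on analgesia during labor as an alternative nonpharmacological intervention". It names no stage, change score or summary.
- **Hypotheses.** Against a null of similar effect there are two directional alternatives: "Hypothesis 1: the use of LED photobiomodulation exerts an analgesic effect superior to that of the bath therapy" and "Hypothesis 2: the use of LED photobiomodulation exerts an analgesic effect inferior to that of the bath therapy".
- **Sample size.** Section 2.3 uses one difference and names no stage: "The difference in the mean VAS score between the groups was set as 2 (standard deviation: 1.6").
- **Analysis.** Section 2.7: "The distribution of the VAS scores will be analyzed, and the continuous variables with normal data distribution will be compared using the" t test. Then: "Non-normal data will be analyzed using the" Mann-Whitney U test. All analyses are "at a level of significance of 5" percent.

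The article mentions no summary over stages, order of testing, adjustment for three comparisons or use of the baseline score.

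**The concern.** The trial asks one question and collects three answers to it. The t test and Mann-Whitney U each need one value per woman, and the article does not say what that value is. The objective, the hypotheses and the sample size are the three places where the deciding score could be fixed, and none of them fixes it.

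This matters because the stages may well differ. The Introduction cites a systematic review in which the hot bath reduced pain at 8 to 9 cm, so a control effect that varies by stage is foreseeable. LED could look better at one stage and no different, or worse, at another. Section 2.2 would allow any of these to be read as the trial's result. If the choice can be made after the data are seen, the 5% level no longer describes the risk of a false claim.

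The baseline score is also collected and then not used, although adjusting for it is a simple way to make the group comparison more precise.

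**Working it through.** **Inputs**
- From the article: 3 post-intervention scores (2.1); 5% for every analysis (2.7); difference 2 and SD 1.6 (2.3); 30 women per group (2.1, 2.3).
- Inferred: tests are two-sided, because both directions are hypotheses.
- Assumed: a correlation rho between the scores of the same woman at different stages. The article gives none, so a range is shown. With the same women in each test, rho is also the correlation between the three test statistics.
- Scenario, inferred and not stated: each stage is tested separately and any one significant result can support a claim.

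**The plan's own figure.** The only error rate stated is 5% per analysis. A single prespecified comparison reproduces it: P(|Z| > 1.96) = 5%. No overall rate for the three scores is given.

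**Step 1: independent tests.** 1 - (1 - 0.05)^3 = 1 - 0.857 = 14.3%.

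**Step 2: equally correlated tests.** With c = 1.96, standard normal density phi and distribution function Phi,

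P(at least one) = 1 - integral of phi(u) x [Phi((c - sqrt(rho) u)/sqrt(1 - rho)) - Phi((-c - sqrt(rho) u)/sqrt(1 - rho))]^3 du.

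| rho | Formula | Simulated t tests, 30 per group, equal correlation |
|---|---|---|
| 0 | 14.3% | 14.2% |
| 0.3 | 13.6% | 13.6% |
| 0.5 | 12.5% | 12.9% |
| 0.7 | 10.9% | 10.9% |
| 0.8 | 9.8% | 9.7% |
| 0.9 | 8.4% | 8.4% |

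The simulations used 40,000 runs each. The rate crosses 10% at rho of about 0.79. If correlation instead fades with distance between stages (AR(1)), the simulated rate is 10.2% at 0.8 and 8.8% at 0.9. It reaches 5% only at rho = 1.

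**Step 3: one direction only.** A false claim of superiority alone is at most 3 x 2.5% = 7.5%. With independent tests it is 1 - 0.975^3 = 7.3%, against 2.5% for a single test.

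**Step 4: would control of the error cost power?** The standardised difference is 2/1.6 = 1.25. With 30 per group, one test at 5% has power above 99%. Even a Bonferroni split (0.05/3 = 0.0167 per stage) leaves about 99% per stage, with an overall error of at most 5% (4.9% at rho = 0, 4.5% at 0.5). On the protocol's own inputs the present sample is therefore enough for either approach. (The stated minimum of 28 does not follow from those inputs. That is a separate matter and does not affect this point.)

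**The case against.** The strongest reply is that the problem lies in what the article leaves unsaid. Only a condensed article is at hand, and a covariance structure, a multiplicity rule and the handling of missing scores commonly sit in a fuller document. That is fair, and none of those absences is charged here. What stands is narrower: the article does commit to an objective, hypotheses, a sample size, named tests and a level, and together they do not identify the comparison that decides.

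Several stronger readings are tempting and should be resisted:

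- **That two-sample tests must be run stage by stage.** They need not be. A t test or Mann-Whitney test works on one value per woman, such as her mean score or her last score. Section 2.7 does not say that stages are tested separately.
- **That any one significant stage counts.** No section says so. If all three stages had to agree, the error would be no more than 5%.
- **That the error exceeds 10% outright.** It does so only under the scenario above and below a correlation of about 0.79, and the article gives no correlation.
- **That women who miss a stage through fast labour make each test a selected sample.** This is plausible, but nothing in the article describes or quantifies it.
- **That averaging is worth 50% more women.** The variance of a three-score mean is (1 + 2 x rho)/3 of a single score's, if variances are equal. At rho = 0.5 that is 0.67, and 1/0.67 = 1.5; at rho = 0.8 it is 0.87, a gain of only 15%. The figure rests on an assumed correlation, and power on the stated inputs is already very high.

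**Conclusion.** The point holds in a conditional form. As a matter of record, section 2.7 names no single deciding comparison among three post-treatment pain scores and does not use the baseline VAS. The size of the resulting error depends on practice that the article leaves open. If stages are tested separately and any one can carry the claim, the chance of at least one false significant result is about 11-14% for assumed correlations up to 0.7, about 8-10% at 0.8-0.9, and above 5% at any correlation below 1. These figures count errors in both directions together.

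The article does not show that the trial will be analysed in that way. The case for change is that a clearly better primary analysis is available from data already planned, holds the 5% level whatever the correlation, and costs almost nothing.

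**What to change.** In section 2.7, state one primary comparison: the group difference in post-intervention VAS averaged over the three stages and adjusted for baseline VAS, tested two-sided at 5%. Tie the objective in 2.2 and the difference in 2.3 to the same quantity.

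Choose one of two forms in advance:
- a repeated-measures mixed model on the three scores, with group, stage, group-by-stage interaction and baseline VAS; or
- an ANCOVA of each woman's mean score on group and baseline VAS.

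Keep the Mann-Whitney U test, applied to each woman's mean score, as the sensitivity analysis for non-normal data. Report the three stage-specific differences with 95% confidence intervals as secondary results.

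The cost is wording only: no new data, visits or participants. There are two downsides. An effect confined to one stage is no longer a stand-alone primary claim. Women with a missing stage are handled under a missing-at-random assumption, which should be stated; the mean-score form also needs a rule for forming the mean when a stage is missing. If the investigators do want a claim at each stage, testing each at 0.0167 is a simpler alternative that also keeps the overall error at or below 5%.

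### Baseline VAS is recorded, but the tests named for the outcome cannot adjust for it; ANCOVA would give narrower intervals for almost no cost

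*Protocol article*

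**What the plan says.** Section 2.1 (and the Abstract) provides for a pain score before treatment: "visual analogue scale (VAS) with a score from 0 to 10 at baseline, that is, before the intervention". It then provides for the outcome scores: "At the 3 time points, the level of pain will be assessed using VAS shortly after the intervention". The three time points are dilation windows of 4–5, 6–7 and 8–9 cm.

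Section 2.7 fixes the tests. After the distribution of the VAS scores has been examined, "the continuous variables with normal data distribution will be compared using the" t test. Otherwise, "Non-normal data will be analyzed using the Mann–Whitney" U test. All analyses are at the 5% level. The section names no covariate, change score, ANCOVA or repeated-measures model.

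Section 2.3 sizes the trial on a difference in means: "The difference in the mean VAS score between the groups was set as 2 (standard deviation: 1.6"). It plans 30 women per group.

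**The concern.** A pre-treatment measurement of the outcome variable is usually the most useful covariate a trial has, and this trial already collects it. The named tests compare two groups on one variable and have no place for it. Two things follow.

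- Variation in the outcome that starting pain could explain stays in the error term, so the confidence interval is wider than it needs to be.
- If the arms happen to differ in starting pain, part of that difference passes into the estimated effect. Section 2.4 describes 1:1 randomization in blocks of six and mentions no stratification, so nothing stated in the design or the analysis corrects for it.

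A related weakness is that the choice between t test and Mann–Whitney depends on the observed distribution. The trial is sized on a mean difference, but a Mann–Whitney test alone gives no estimate on that scale. What is being estimated should not depend on a normality check.

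**Working it through.** **Inputs from the article.** Difference 2 and SD 1.6 (section 2.3); 30 per arm (sections 2.1 and 2.3); alpha 5%, taken as two-sided because section 2.2 lists both a superior and an inferior alternative.

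**Assumed inputs.** The correlation ρ between baseline and post-session VAS is not given, so I use 0.3, 0.5 and 0.7. The baseline SD is not given either; I take it as 1.6, equal to the sizing SD, which makes the regression slope equal to ρ.

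**The plan's own figure.** The article gives a minimum of 28 for 80% power and does not say whether this is per group or in total. The normal approximation gives n per arm = 2 × 1.6² × (1.96 + 0.84)² / 2² ≈ 10.0, rounded up to 11 because the unrounded value is just above 10. That is 22 in total; the exact t-test calculation gives 12 per arm, or 24 in total. The 28 is therefore not reproduced either way. That is a separate matter and does not affect what follows, which uses the 30 per arm.

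**Unadjusted comparison.**
- SE = 1.6 × √(2/30) = 0.413.
- Power at a difference of 2 = Φ(2/0.413 − 1.96) = Φ(2.88) ≈ 99.8%.
- Difference detectable at 80% power = 0.413 × (1.96 + 0.84) = 1.16.

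**Adjusted comparison.** ANCOVA residual SD = 1.6 × √(1 − ρ²). The formula ignores the small cost of estimating one slope.

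| Analysis | Variance factor | Residual SD | SE | Detectable at 80% power | Power at an assumed difference of 1 |
|---|---|---|---|---|---|
| Unadjusted | 1 | 1.600 | 0.413 | 1.16 | 68% |
| ANCOVA, ρ = 0.3 | 0.91 | 1.526 | 0.394 | 1.10 | 72% |
| ANCOVA, ρ = 0.5 | 0.75 | 1.386 | 0.358 | 1.00 | 80% |
| ANCOVA, ρ = 0.7 | 0.51 | 1.143 | 0.295 | 0.83 | 92% |

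With a t multiplier of about 2.00, the 95% CI half-width is 0.83 unadjusted, and 0.79, 0.72 and 0.59 adjusted.

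**If change scores were meant.** With equal variances, the change-score SD is 1.6 × √(2(1 − ρ)): 1.893, 1.600 and 1.239 at ρ = 0.3, 0.5 and 0.7. Each is larger than the ANCOVA residual SD. Below ρ = 0.5, change scores are also noisier than raw post-session scores.

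**Chance imbalance.** The baseline difference between arms has SD 1.6 × √(2/30) = 0.413, so it exceeds 1.96 × 0.413 = 0.81 points, in one direction or the other, in about 1 trial in 20. The unadjusted estimate then moves by ρ × 0.81 = 0.24, 0.41 or 0.57 points. The middle value is about one standard error, or one fifth of the planned difference.

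**The case against.** The strongest case against has four parts.

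- **The wording does not say that post-session scores are compared.** This stands. Section 2.7 speaks only of VAS scores and continuous variables. The post-session reading is natural because section 2.3 plans on a difference in mean VAS score, but a t test on change from baseline would also fit the text. The point survives, because a change-score analysis uses baseline less efficiently than ANCOVA.
- **An article may leave covariates to a fuller document.** This would answer a complaint that detail is missing. Here the article names its tests, and the point is that a better method than the named one is available from data already planned.
- **Nothing is invalid.** This stands. A reader might infer bias or an inflated type I error, but randomization keeps the unadjusted test valid, and its standard error already allows for chance imbalance. The loss is one of precision and of error conditional on the imbalance that occurs. Section 2.1 excludes and replaces women who receive drug analgesia, which raises a separate question about who is compared; adjustment does not cure it.
- **The planned conclusion is not at risk.** This also stands. A reader might infer an underpowered trial, but on the article's own inputs power is about 99.8% without adjustment.

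Three further inferences go beyond the text. A large imbalance is possible, not likely. The article does not say how much labor pain varies between women, beyond the sizing SD of 1.6. A mean test at one window and a rank test at another would be allowed by section 2.7, but it does not say that the check is made window by window.

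**Conclusion.** The point holds as a worthwhile improvement to the stated analysis, not as an error that invalidates it. The named tests cannot adjust for a baseline that is already collected. The gain from adjusting is a variance reduction of 9%, 25% or 51% at assumed correlations of 0.3, 0.5 or 0.7. It shows in narrower intervals, in better power for effects smaller than the planned 2 points, and in removing the influence of chance imbalance in starting pain.

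The size depends on a correlation that the article does not give. Baseline is taken before the intervention while outcomes run to 8–9 cm, so the correlation may be weak for the later windows, and the gain there may be small. The imbalance figures also rest on the assumed baseline SD of 1.6. The choice of test by observed distribution is a secondary weakness, for which no size can be given from the article.

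**What to change.** In section 2.7, make the primary VAS comparison an ANCOVA with baseline VAS as covariate, or a mixed model over the three dilation windows with the same covariate. State that the analysed variable is the post-session score. Report the adjusted mean difference with its 95% CI whatever the normality check shows, and keep Mann–Whitney as a named sensitivity analysis.

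The cost is a change of analysis wording and one degree of freedom, with no new data or visits. If the correlation proves low, little is gained and very little is lost. The change should be made before any outcome data are examined by arm.

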## Discussion

3

This study describes the protocol for a randomized controlled clinical trial aimed to evaluate the effect of LED therapy on analgesia during labor. The advantages of using LED therapy for analgesia during labor include the ease of application, the feasibility of application by the same team that assists the patient during labor, the possibility of the patient choosing the position that feels the most comfortable, even under analgesia, and improved mobility; the patient can remain in the upright position to help the fetal descent.

The main contribution of this clinical trial is the development of an analgesic intervention during labor that is effective and accessible for use in various public and private health services. The findings of this study may help develop protocols for analgesia during labor, thus allowing patients to not be afraid of pain and promote vaginal delivery.

This study will be the first to use photobiomodulation for analgesia during labor, and the results may help elucidate the correlation between phototherapy in pregnant women and fetal characteristics during therapy. In case of favorable outcomes, this approach can be used as a noninvasive and nonpharmacological alternative for analgesia during labor.
